## Abstract

**Introduction::**

Ischemic stroke (IS) is the one of the most severe neurological disease, survivors may live with upper limb motor dysfunction (ULMD) resulting in heavy social and economic burden. Nowadays, there are few approaches to promote the rehabilitation of ULMD. Auricular acupuncture (electroacupuncture [EA]) has long been used in the treatment of neurological disorders in China. This treatment has become an attractive treatment option due to its low cost, portability, minimal side effects, and ease of use in clinical and operational environments. However, its efficacy and safety in consciousness recovery remain to be proved.

**Methods::**

A total of 80 IS patients with single upper limb motor function impairment will be recruited in the trial and randomized into EA or control groups. Patients in the control group will receive routine conventional treatment alone while patients in the EA group will receive EA treatment for 3 consecutive weeks based on routine conventional treatment. Baseline evaluation was carried out on day of enrollment, post-treatment evaluation was carried out 14 and 21 days after enrollment, and the 2 groups were follow-ups in 3 and 6 months after the end of the trial. The efficacy will be assessed with the changes in the upper limb Fugl–Meyer assessment, Wolf motor function test, action research arm test, active range of motion, and Barthel index. The safety of EA will be estimated by monitoring the incidence of adverse events and changes in vital signs during the study period. Analysis of feasibility will be descriptive and the change in outcome measures between groups will be analyzed using an independent sample *t* test.

**Discussion::**

This study tried to narrow the evidence gap on the efficacy of EA at the auricular on the recovery of ULMD in patients with IS. The results of this trial will provide strong evidence for the efficacy and safety of EA of auricular concha region stimulation for IS patients.

**Trial registration:** This trial has been registered at the Chinese Clinical Trial Registry, numbered ChiCTR2100049678.

## Introduction

1

Ischemic stroke (IS) is a leading cause of mortality and morbidity worldwide, which associated with the disability and increases the social economic burden.^[1]^ The upper limb motor dysfunction (ULMD) is widespread around the patients and has been thought to be common after IS, which is considered to be in need of treatment.^[2]^ Thus far, approximately 85% of patients with ULMD after IS have arm weakness as well as 60% of survivors with non-function arms cannot recover function within 6 months.^[3,4]^ At present, comprehensive rehabilitation programs had been being used to the rehabilitation of ULMD such as neuromuscular electrical stimulation, forced exercise therapy, occupational therapy, imagination therapy, and rehabilitation robots.^[5]^ However, the implementation of the above-mentioned treatment strategies for ULMD should be moderate.^[6]^ New and more effective treatment methods need to be considered.

Acupuncture has been used for over 2000 years in China. As a complementary and alternative management for neurological disease, including IS, acupuncture is popular all over the world for features of easy operation and safety.^[7]^ Auricular acupuncture (AA) is an important part of Chinese acupuncture. The Yuan Dynasty Weisheng Baojian believed: “five viscera and six bowels, twelve meridians and collaterals coverage in the ear.”^[8]^ AA therapy can not only adjust the mind directly, but also cooperate with the ear or indirectly stimulate the 5 viscera (heart, liver, lung, spleen, and kidney) by stimulating the auricular concha area (ACR), so as to realize the harmoniousness of heart-brain and balance Qi and blood.^[9]^ Animal studies found that electroacupuncture (EA) at ACR (EA-ACR) had significant effects in the management of primary hypertension,^[10]^ diabetes,^[11]^ and partial epilepsy.^[12]^ EA-ACR is a noninvasive procedure that requires a portable EA device with less side effects. However, clinical evidence on its efficacy is controversial due to problems concerning the study design, including small sample size, high drop-out rate, lack of proper control, and high/unclear risk of bias.

Therefore, we intend to evaluate the efficacy and safety of EA-ACR in the recovery of ULMD in patients with IS. Furthermore, we hope that this trial will provide high-quality evidence for the application of EA-ACR in the management of IS patients as well as to establish a standard acupuncture procedure for clinical practice.

## Methods

2

### Study design

2.1

Here, we design a blinded, randomized controlled trial, 80 patients with ULMD after IS were recruited by clinicians. The EA treatment protocol was determined according to reference and results of previous research on EA treatment for ULMD. All participants will go through a standardized interview and be provided with details of the study. The acupuncturists who deliver treatments for EA groups are registered with the Ministry of Health of the People's Republic of China as Chinese medicine practitioners and have >10 years of clinical experience.

In addition to routine treatment, patients in the EA group will receive EA treatment for 3 consecutive weeks. Patients in the control group will receive routine treatment alone. The research process is shown in Fig. 1.

**Figure 1 F1:**
[figure not shown]
Flow chart of the study procedure.

### Sample size

2.2

The sample size was calculated according to the following formula:

$$\text{N}=\frac{{\left[{\text{u}}_{\alpha }\sqrt{2\text{p}(1-\text{p})}+{\text{u}}_{2\beta }\sqrt{{\text{p}}_{1}(1-{\text{p}}_{1})+{\text{p}}_{2}(1-{\text{p}}_{2})}\right]}^{2}}{{\left({\text{p}}_{1}-{\text{p}}_{2}\right)}^{2}}$$

when the significance level is *α* = 0.05, *β* = 0.10, N is the required sample size for each group. Calculated by the formula: N = 32. There may be the probability of missing to follow-up and termination of various reasons among the subjects. Thus, allowing for 10% to 15% of attrition, the sample size should be adjusted N = 40, that is, each group 40 patients, so the sample size of the 2 groups of patients is determined to be 80 cases.

### Inclusion criteria

2.3

(1)Aged 18 to 80 years old;(2)have cerebral infarction with a first onset and onset >6 months;(3)the previous physical activity was normal, and there were different degrees of hemiplegia in admission;(4)vital signs are stable;(5)Mini-Mental State Examination (MMSE) score ≥22 and compliance with the interventions;(6)can take the secondary prevention drugs for cerebral infarction and patients with routine rehabilitation training;(7)written informed consent of the patient or their legal guardian has been obtained.

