AA is a form of acupuncture that originated in China.^[17]^ The practice of AA is mentioned in the Yellow Emporer's Classic of Internal Medicine, one of China's oldest medical classics. In this book, Yang meridian, 5 viscera and 6 bowels and kidney are documented as directly connected to the ear.^[18]^ The heart is the organ similar to the monarch and is responsible for spirit and mental activity.^[19]^ The heart, located where the “spirit” (shen) resides, opens into the ear and governs the blood according to TCM.^[20]^ “Regulating the heart, treating collaterals from the heart, nourishing the heart and dredging collaterals."^[21]^ CO15 (Xin) was often used as corresponding channel point selection for sequelae of stroke.^[22,23]^ EA at CO15 (Xin) could activate the cervical vagus nerve, increasing the discharge activity of the nucleus tractus solitarius of the ascending nucleus of the vagus nerve.^[24]^ Horseradish peroxidase (HRP) nerve tracer was injected into the auricle area for tagging neurons, which could be found that tagged neurons appear in nuclei such as the nucleus tractus solitarius and the dorsal motor nucleus of the vagus nerve.^[25]^ Study showed that non-invasive electrical stimulation of the ACH, aiming to activate vagal afferences, appeared to be beneficial to the recovery of upper limb motor function in subacute IS patients.^[26]^ AT4 (Pizhixia) can regulate the central nervous system, inhibit the excitability of the cerebral cortex and autonomic nerve center, which have the functions of relieve mental strain and regulating viscera.^[22]^ AT4 (Pizhixia) is commonly used to treat stroke also have a certain degree of efficacy in relieving post-stroke pain and reducing inflammatory response.^[27]^ The Kidney was the “Sea of Marrow” and relate to the brain in TCM. The Kidney energetic organ system is in charge of storing Essence or Jing; abundant Essence results in normal hearing as the Ling Shu explains, “… depletion of Essence gives rise to deafness.”^[28]^ The liver controls the smooth flow of Qi throughout the body. If wood imbalances are not properly addressed, Qi stagnation can develop. Since blood circulation depends on Qi circulation, blood stasis can result. Sudden onset of ear pain or tinnitus, sudden deafness can result from blood stagnation due to Qi stagnation.^[29]^ Herein, our study selected EA to stimulate CO15 (Xin), AT4 (Pizhixia), CO10 (Shen), and CO12 (Gan) based on preliminary foundation and clinical research results.

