The present study still has some unavoidable limitations. First, despite assessor-blinding, patients cannot be blinded due to the nature of EA manipulation, which may lead to the occurrence of performance and detection biases. Second, as this study is intended as a pilot study for further larger clinical studies, sample size is another limitation.

In conclusion, this study will provide solid evidence of the role of EA-ACR in the recovery of ULMD of IS patients.

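### Entry is limited to patients more than 6 months after a first infarction, but the only cited clinical arm-function result is in subacute patients and the conclusions are worded for ischemic stroke of any stage

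*Protocol article*

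**What the plan says.** **Entry.** Section 2.3, criterion (2), admits patients who "have cerebral infarction with a first onset and onset >6 months". I read the first part as first-ever stroke. No upper limit is set, and no other section gives a time window. Criterion (3) adds that "there were different degrees of hemiplegia in admission", again without a time. Section 2.4 excludes lacunar and hemorrhagic infarction.

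**Evidence.** Section 3 cites one clinical result on electrical stimulation of this ear region and arm function. That stimulation was non-invasive and "appeared to be beneficial to the recovery of upper limb motor function in subacute IS patients". The rest of the rationale is of other kinds. It includes traditional theory, nerve-tracing work and customary use of points ("CO15 (Xin) was often used as corresponding channel point selection for sequelae of stroke"). Section 1 adds work in other diseases: "Animal studies found that electroacupuncture (EA) at ACR (EA-ACR) had significant effects in the management of primary hypertension", with diabetes and partial epilepsy named alongside.

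**Claims.** The objective in section 1 is "we intend to evaluate the efficacy and safety of EA-ACR in the recovery of ULMD in patients with IS". The abstract promises strong evidence "for the efficacy and safety of EA of auricular concha region stimulation for IS patients", and section 3 closes with "this study will provide solid evidence of the role of EA-ACR in the recovery of ULMD of IS patients". The registered title in section 2.14 carries no stage either.

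**Limitations.** Section 3 lists two: patients cannot be blinded, and the sample is that of a pilot.

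**Analysis.** Section 2.12 compares change in the outcome measures between groups with an independent-sample t test, or a rank test if the data are not normal. It names no covariate.

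**The concern.** The entry rule, the supporting clinical result and the claim refer to three different populations: patients beyond 6 months, subacute patients, and ischemic stroke patients of any stage. The document does not remark on the difference.

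The introduction itself uses 6 months as a reference point for arm recovery, so stage is not a trivial descriptor here. If the report keeps the present wording, a positive result could be applied to early patients, none of whom can be enrolled. A null result could be taken as evidence against the technique in ischemic stroke generally, although the stage of the one cited benefit was not studied. The introduction also hopes to establish a standard procedure for clinical practice, which makes the scope of the conclusion matter.

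**Working it through.** The plan gives no figure of its own on this point, and the sample-size calculation in section 2.2 does not bear on it. The main check is to set the statements side by side.

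| Element | Place | Time since stroke |
|---|---|---|
| Eligible patients | 2.3, criterion (2) | more than 6 months, no upper limit |
| Cited clinical arm-function result | 3 | subacute |
| Objective | 1 | not restricted |
| Conclusions | Abstract; 3 | not restricted |
| Limitations | 3 | not mentioned |

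**Step 1: overlap of enrolled patients with the cited evidence.** Section 2.6 allocates 40 + 40 = 80 patients, all subject to criterion (2). The article does not define subacute. On the assumption that it ends before 6 months, 0 of 80 come from the stage of the cited result.

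**Step 2: how much of the named population is left out.** This would need the distribution of patients with arm impairment by time since stroke, which the document does not give. The one related figure, in section 1, is that 60% of survivors with a non-functional arm have not regained function within 6 months. It suggests that late patients are a substantial group. It gives no share of all patients.

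**Step 3: time since onset in the comparison.** For any baseline variable, with 40 per arm, the standard deviation of the between-arm difference, in units of that variable's SD, is

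sqrt(1/40 + 1/40) = sqrt(0.05) = 0.224.

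The chance of a difference above 0.3 SD in either direction is 2 × [1 − Φ(0.3/0.224)] = 2 × [1 − Φ(1.34)], about 0.18. This holds for every covariate in any trial with 40 per arm. It is not specific to time since onset.

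**Step 4: what adjustment would gain.** If baseline FMA-U and months since onset together explain a fraction R² of the variance of change within arms, the standard error of the treatment difference is multiplied by about sqrt(1 − R²), apart from a small loss of degrees of freedom. The document gives neither R² nor an SD for FMA-U, so the gain cannot be put in numbers.

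**The case against.** The case on the other side is substantial. Eligibility criteria are where a protocol defines its population, and this one does so openly. Titles and objectives are shorthand: this objective also omits the age range, the MMSE threshold and the exclusion of lacunar infarction. Studying patients beyond 6 months, without an upper limit, is a legitimate choice. All of that stands. What remains is that the concluding claims and the limitations are where a reader looks for scope, and neither mentions the restriction.

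Four stronger readings are tempting, and the document does not support them.

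- **That the trial cannot answer its objective for most of the population it names.** No figure supports the word most (step 2), and a randomised comparison in late patients is valid for late patients.
- **That the whole rationale is subacute, or that the trial tests a subacute hypothesis.** The subacute study is one strand among several. It used non-invasive stimulation, whereas section 2.8.2 inserts needles. Section 2.1 also rests the regimen on previous research in arm dysfunction whose stage is not stated.
- **That the 6-month limit is a slip.** No section gives a conflicting window. The reference to hemiplegia at admission is at most suggestive, so the sponsor can only be asked to confirm.
- **That the 18% chance of imbalance biases the result.** Chance imbalance is already allowed for in the error rate of a randomised test.

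It is also fair to say that covariates are commonly settled in an analysis plan, which is not at hand, and that Table 1 is not shown. Months since onset may well be recorded, since criterion (2) cannot be applied without knowing the onset date. The covariate is therefore offered as an improvement. Its absence is not counted as an error.

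**Conclusion.** The point holds as a mismatch of scope. The design supports a conclusion about first-ever, non-lacunar ischemic stroke more than 6 months after onset. The article states a conclusion about ischemic stroke patients without a stage, cites clinical arm-function support only from a stage it appears to exclude, and does not list the restriction as a limitation.

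The mismatch affects how far the result may be carried. It does not affect the internal validity of the comparison or its type I error. The verdict rests on two assumptions: that criterion (2) is printed as intended, and that subacute ends before 6 months. If the first fails, the passages still need reconciling, but the scope of the claim would have to follow the corrected window. Which window is right cannot be decided from the document, and no view is taken on it.

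**What to change.** 1. **Confirm criterion (2)** and reconcile it in section 3 with the subacute result. If it stands, say that this evidence does not carry over directly to the patients enrolled. If it is an error, correct it before analysis and report how many patients entered under each rule. Section 2.14 gives June 2022 as the end of the study, so this may have to be done in the results report.
2. **Limit the objective (section 1) and the conclusions (abstract and section 3)** to first-ever, non-lacunar ischemic stroke within the enrolled time window.
3. **List the restriction as a limitation** beside patient blinding and sample size.
4. **Report months since onset by arm.** For FMA-U, replace the unadjusted t test on change with a linear model containing treatment, baseline FMA-U and months since onset. Fix the scale of the time variable in advance, because without an upper limit it may be skewed. Describe this as a modest gain in precision, not as a correction of bias.

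Items 1 to 3 cost only wording. Item 4 needs one item from the history, which is already required to apply the entry rule, and slightly more analysis work. The downside is a narrower claim.

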### Exclusion criteria

2.4

(1)Hemorrhagic cerebral infarction, lacunar infarction;(2)relatively severe systemic diseases (severe cardiovascular disease, respiratory, digestive, urinary system dysfunction, and hematopathy);(3)malignant tumors or various infectious diseases;(4)patients with locomotor system and other diseases affect muscle strength assessment;(5)patients who cannot be combined with rehabilitation assessment.

### Participant recruitment

2.5

Patients who meet our eligibility criteria will be screened consecutively from Department of Rehabilitation Medicine, The Second Affiliated Hospital of Chongqing Medical University. Researchers will screen the list of patients every other day, continue to recruit and monitor recruitment. Eligible patients will be screened, oral and written information about the study will be obtained from the researchers later. After signing the informed consent form, demographic and clinical characteristics will be measured (baseline assessment, t0). Weekly recruitment statistics will be discussed to improve the recruitment process. On this basis, if necessary, the research team discussed updates to recruitment and retention strategies.

### Randomization and allocation concealment

2.6

The randomization sequence will be generated by computer using SPSS 26.0 (IBM, USA). All participants who meet the inclusion criteria will be randomly assigned to an intervention group or control group (40 cases each) at a 1:1 ratio. Opaque computer-generated sealed envelopes will be produced to cover the distribution. The envelope will be serially numbered with a serial number on the outside and will contain distribution information on the inside. Upon completion of baseline assessment and written informed consent, the subject will be enrolled in the study, at which time the envelope will be opened. Participants will be assigned to one of the two groups and receive related interventions. The random distribution sequence and the opaque sealed envelope will be kept separately by 2 specific researchers.

### Blinding

2.7

Each participant was initially interviewed and evaluated by a clinician, and the evaluation was then confirmed by another well-trained and experienced clinician. The evaluators, outcome assessors, and statisticians will be blinded to the group allocation and all of them will work independently and separately. It is a pity that patients could not be blinded in this study.

### Interventions

2.8

#### Selected principles of acupuncture point

2.8.1

We selected the auricular acupoints of The Five Viscera (Yin Organs) and Six Bowels (Yang Organs), tissues and organs related to the etiology and mechanism of stroke in traditional Chinese medicine (TCM), as well as the relevant auricular acupoints of the pathogenesis sites and associated systems in modern medicine, including CO15 (Xin), AT4 (Pizhixia), CO10 (Shen), and CO12 (Gan). Acupoint positioning is based on National Standards of People's Republic of China: name and location of ear acupoints (GB/T 13734-1992).^[13]^

#### Treatment group

2.8.2

Figure 2 shows the schematic sites of acupuncture points in EA group. Sterilized needles (the acupuncture needles of 0.30 mm in diameter and 25 mm in length [Suzhou Hualun Medical Appliance Co. Ltd., China]) will be used. Acupuncture is inserted vertically, inserted at a depth of about 0.1 to 0.3 cm, and the electrical stimulation device is connected after Deqi sensation. The parameters were selected as follows: 20 Hz square wave, current intensity 0.5 mA, each lasting 30 seconds, stimulating once every 5 minutes. The participant could withdraw from the trial if he could not tolerate the stimulation. Stimulation was performed for 30 minutes per day for 3 consecutive weeks.

**Figure 2 F2:**
[figure not shown]
Schematic sites of acupuncture points in EA group.

#### Control group

2.8.3

Participants who are assigned to the control group will receive routine rehabilitation training, which is customized according to the patient's abilities and applied to the limbs and trunks, involving postural control, turn over regularly, joint mobility training, muscle strength training, and always at the upper limit of their capacity.

#### Follow-up

2.8.4

All patients will receive evaluation at 0 days after enrollment, 14 and 21 days after post-treatment, and 3 and 6 months at the end of the trial. Scoring data are collected, as described in Table 1.

**Table 1 T1:**
[figure not shown]
Schedule of enrollment, interventions, and assessments.

### Outcomes

2.9

#### Primary outcome

2.9.1

#### Secondary outcomes

2.9.2

##### Wolf motor function test

2.9.2.1

Wolf motor function test (WMFT) focuses on evaluate the rehabilitation scale of ULMF after stroke. The design of the WMFT ranges from simple to complex, including proximal and distal joints, to test the quality and speed of the upper limb movement. It can quantitatively evaluate the exercise ability of the patient's upper limbs by timing single joint movement, multi-joint movement, and functional activity and evaluating the quality of exercise. WMFT consists of 15 projects, and 6-point scale ranging from 0 to 5 (normal).

##### Action research arm test

2.9.2.2

Action research arm test has a total of 19 test items, divided into 4 groups of subscales: Grasp, Grip, Pinch, and Gross Movement. Action research arm test has been regarded as an effective method for assessing specific arm activity limitations which can assess the participant's ability to handle objects of different sizes, weights, and shapes.

